### Randomization and Allocation Concealment

Central randomization will be conducted at the coordinating center. Participants will be randomly allocated in a 1:1 ratio to receive either intravenous dexamethasone or placebo using a computer-generated randomization sequence. Variable block sizes of 4 and 6 will be used, with stratification based on baseline GCS score (≤8 and >8) to ensure balance between the treatment groups. Allocation concealment will be ensured using the Sequentially Numbered Opaque Sealed Envelopes method.

The study medications (dexamethasone or placebo) are prepared in identical-looking vials and labeled with a 5-character alphanumeric code using a randomly generated sequence, as shown in Figure 2. They are securely packed in designated boxes for each site. The random sequence used for labeling the study medications is stored in a password-protected Microsoft Excel sheet, accessible only to an unblinded investigator at the primary site to ensure confidentiality and maintain blinding throughout the study.

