### Data Analysis Plan

#### Summary Statistics

Continuous data will be expressed as the mean and SD, or the median with an IQR. Categorical data will be expressed as percentages. The independent variables in the study include both continuous and categorical factors. Continuous independent variables are age, mean arterial pressure, GCS at admission, time interval between the incident and presentation, admission blood glucose level, and GOS at discharge and on day 28. The categorical independent variables include sex, type of hanging (complete or partial), material used for hanging, presence of seizures, hanging-induced cardiac arrest, requirement for mechanical ventilation, vasopressor support, and in-hospital complications. The dependent variables consist of both continuous and categorical outcomes. The continuous dependent variable is the duration of hospital stay, while the categorical dependent variables include the proportion of patients with a good neurological outcome at discharge and on day 28, as well as the occurrence of in-hospital complications.

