#### Analytical Statistics

The primary and secondary outcomes will be compared between the intervention and placebo groups using appropriate statistical tests. The proportion of patients achieving good neurological outcomes on day 28, as well as the proportion achieving good neurological outcomes at discharge, will be analyzed using the chi-square or Fisher exact test, with results expressed as relative risk estimates. Similarly, the comparison of in-hospital complications between the 2 groups will also use the chi-square or Fisher exact test, with relative risk used to quantify the effect size. For continuous outcomes, such as the duration of hospital stay, comparisons will be made using either the independent *t* test or the Mann-Whitney *U* test depending on data distribution, and the effect will be reported as an absolute difference between groups.

The primary efficacy analysis will be carried out by following the intention-to-treat principle. A per-protocol analysis will be performed as a secondary analysis. If there are missing data for the outcome at day 28, multiple imputation using chained equations will be used, based on the assumption that data are missing at random [26]. The primary analysis will also adjust for GCS stratification at baseline using a multivariable regression model. No adjustment for study site will be carried out, as all the sites have a similar profile with respect to available treatment and manpower. All statistical analyses will be carried out at a 5% level of significance, and a *P* value <.05 will be considered significant. For interim analyses alone, *P*<.002 will be applied, following the Haybittle-Peto stopping rule.

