#### Subgroup Analysis

Subgroup analysis will be conducted using the same analytical methods described for the primary and secondary outcome measures, including the subgroup variable and an appropriate effect size measure with a 95% CI.

Subgroup analyses were planned based on key clinical and demographic variables. These included gender (male vs female), severity of neurological impairment as assessed by GCS (≤8 vs>8), and the type of hanging (partial vs complete). Additional subgroup variables comprised the presence or absence of seizures, the presence or absence of cardiac arrest at presentation, and admission blood glucose levels categorized as <140 mg/dL vs ≥140 mg/dL.

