### Limitations

There are a few anticipated limitations to consider; this trial is being conducted at 3 tertiary care centers in India, which may limit the generalizability of the findings to other public and private hospitals or to international populations. The sample size calculation assumed a 20% absolute difference between the treatment groups, which may be considered relatively high. This assumption was made to ensure feasibility within the constraints of the 3-year study period, available funding, and the limited number of near-hanging cases, and it represents a pragmatic compromise between feasibility and statistical power. Short-term follow-up (28 d) is also a limitation.

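### The adjusted primary analysis names only the two-level GCS stratum, so a modest gain in precision from baseline data already recorded is left unused

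*Protocol article*

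**What the plan says.** The protocol article, Analytical Statistics, compares good neurological outcome at day 28 between arms in two ways. The proportions "will be analyzed using the chi-square or Fisher exact test, with results expressed as relative risk estimates". In addition, "The primary analysis will also adjust for GCS stratification at baseline using a multivariable regression model". The section then rules out one covariate: "No adjustment for study site will be carried out, as all the sites have a similar profile". No further covariate is named.

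The stratum is defined under Randomization and Allocation Concealment: allocation is blocked "with stratification based on baseline GCS score (≤8 and >8) to ensure balance between the treatment groups". Eligibility requires GCS ≤13, so each level pools several scores, 3 to 8 and 9 to 13.

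Finer baseline information is already collected. Summary Statistics says "Continuous independent variables are age, mean arterial pressure, GCS at admission" among others, and lists hanging-induced cardiac arrest as a categorical variable. Subgroup Analysis uses "the presence or absence of cardiac arrest at presentation" as a subgroup factor.

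Under Sample Size, 190 to 200 eligible patients are expected, and a substantially larger trial is called infeasible. Under Limitations, the 20-point target difference is conceded to be relatively high: "it represents a pragmatic compromise between feasibility and statistical power".

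**The concern.** A two-level term treats a patient with GCS 3 like one with GCS 8, and one with GCS 9 like one with GCS 13. If outcome varies with the score inside each level, or with cardiac arrest, that variation stays in the residual. Stratified blocks balance only the two levels, so the stratum term cannot correct chance imbalance in exact GCS or arrest within them.

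This trial cannot buy precision with more patients. The Sample Size section also intends to read failure to show a 20-point benefit as evidence against routine steroid use, so a false negative could affect practice. Precision available from data already in hand is therefore worth taking.

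**Working it through.** **1. Reproducing the plan's sample size.** Inputs from Sample Size: 75% vs 55% good outcome, 80% power, 10% attrition. Two-sided alpha is taken as 5%, as in Analytical Statistics. (Sample Size prints 0.05%, which would need 204 per arm, so it is a misprint.)

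n per arm = (z₀.₉₇₅ + z₀.₈₀)² × [0.75×0.25 + 0.55×0.45] / 0.20² = 85.36, rounded up to 86. Then 86/0.9 gives 96 per arm, 192 in total. The stated figures reproduce.

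**2. Power by covariate set.** The documents give no GCS distribution, prognostic strength or arrest prevalence. These are assumptions: GCS uniform on 3 to 13; odds ratio (OR) per GCS point 1.0 to 1.5; OR of arrest for poor outcome 1 to 10; arrest prevalence 10% in the first four rows and 15% in the last two. Each scenario used 2,000 simulated trials of 172 patients, with 1:1 allocation within GCS ≤8 and >8 and overall rates held at 55% and 75%. The regression columns are logistic likelihood-ratio tests. The Monte Carlo standard error is about 0.9 points per cell, and all analyses used the same simulated trials.

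| OR per GCS point / OR for arrest | Chi-square | Stratum | Exact GCS | Exact GCS + arrest | Gain over stratum (points) |
|---|---|---|---|---|---|
| 1.0 / 1 | 79.4% | 79.9% | 80.0% | 80.0% | 0.1 |
| 1.1 / 2 | 80.3% | 80.9% | 81.5% | 81.8% | 0.9 |
| 1.2 / 3 | 78.9% | 80.8% | 81.7% | 82.3% | 1.5 |
| 1.3 / 5 | 80.6% | 83.4% | 84.4% | 85.8% | 2.4 |
| 1.4 / 5 | 81.2% | 84.9% | 86.4% | 88.6% | 3.7 |
| 1.5 / 10 | 80.4% | 85.2% | 87.6% | 90.6% | 5.4 |

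Replacing the stratum by exact GCS gives 0.1 to 2.4 of these points. Tests on the standardized risk difference gave nearly the same gains (80.8% to 81.6% in the second row, 85.2% to 90.5% in the last). With no treatment effect, rejection was 4.2% with the stratum and 4.3% with exact GCS plus arrest.

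**3. Gain expressed as patients.** The equivalent sample-size ratio is [(1.96 + z at new power)/(1.96 + z at old power)]².
- Second row: [(1.96 + 0.908)/(1.96 + 0.874)]² = 1.02, about 4 patients on 172.
- Last row: [(1.96 + 1.317)/(1.96 + 1.045)]² = 1.19, about 33 patients on 172.

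**4. The model recommended here (stratum + linear GCS + arrest).** A separate simulation at 172 patients gave about 1 to 6 points over the stratum alone under prognostic assumptions. When prognosis is a pure step at GCS 8, power went from 84.2% to 83.8%. With no prognostic value it went from 79.6% to 79.5%. Type I error was near 5%.

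**5. Room for the terms.** At the planned rates, poor outcomes number 86×0.45 + 86×0.25 = 60.2. The retrospective GCS ≤13 cohort in the Introduction had 160×0.23 + 41×0.10 = 40.9 poor outcomes among 201, or 20%. That would be about 35 of 172.

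**The case against.** Adjusting for the randomization stratum is standard and valid, and wanting more covariates could be called preference. A reader might infer that the planned analysis is biased or wrong. Nothing in the documents supports that.

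The article does not say that the stratum is the sole covariate, and an analysis plan that is not shown may add others. That is possible. Still, the text states what is adjusted for and what is left out, and the point concerns that stated choice.

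The size of the gain is wholly assumed, and the main scenarios generate outcomes linear in GCS, the form being recommended. This stands as a limit. When prognosis was instead made to step at GCS 8, replacing the stratum by linear GCS lost 0.5 to 1.0 points (for example 82.8% to 81.8%). That is a reason to keep the stratum and add the score to it, and the combined model showed no material loss.

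Arrest may be rare, especially as moribund patients are excluded. At an assumed 5% prevalence and log-odds of -2.5, all arrest patients shared one outcome in about 17% of simulated final analyses and 44% at half that size. A logistic model then has separation, so this objection stands and the plan needs a fallback.

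Finally, the chi-square or Fisher test sits beside the regression without a statement of which decides. More covariates bring no power if the unadjusted test decides. This also stands.

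**Conclusion.** The point holds as a modest missed efficiency. The one covariate named is a two-level cut of a score that the trial records in full, and a second plausible prognostic factor is recorded but not used in the model. Under the assumed prognostic strengths, the fuller model adds about 1 to 6 power points over the stratum model. Exact GCS alone gives about 0 to 2, and cardiac arrest most of the rest where prognosis is strong. With no prognostic value, essentially nothing is lost.

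A reader might infer that a large amount of power is being discarded, worth as much as 27% more patients. That figure needs an extreme prognostic scenario (87.0% to 93.5% power), and the documents give no prognostic figures to support it. The stratum term already captures roughly half of the gain over the chi-square test (in the 1.3 / 5 scenario, 2.8 of 5.2 points). Any benefit depends on the adjusted result being the deciding one.

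**What to change.** In Analytical Statistics, state that:

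- the adjusted primary model contains treatment, the GCS randomization stratum, the baseline GCS score as a linear term, and cardiac arrest before randomization (yes/no);
- if the arrest term is too sparse or separates, a fallback chosen in advance applies: drop the term, or use a penalized fit;
- the effect is reported as a standardized relative risk, which keeps the planned measure, together with a standardized risk difference;
- this adjusted result is the deciding primary analysis, and the chi-square or Fisher result is supportive.

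The arrest covariate should be limited to events before randomization, because arrests during the study are collected as adverse events.

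The list should be fixed before the interim analysis at 50% enrolment. Three patients had been enrolled when the article was submitted, so there is time.

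The cost is a few sentences and slightly more analysis work, with no new data, visits or patients. The remaining risk is a sparse arrest term if poor outcomes are fewer than planned, which the fallback covers.

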#### Subgroup Analysis

Subgroup analysis will be conducted using the same analytical methods described for the primary and secondary outcome measures, including the subgroup variable and an appropriate effect size measure with a 95% CI.

Subgroup analyses were planned based on key clinical and demographic variables. These included gender (male vs female), severity of neurological impairment as assessed by GCS (≤8 vs>8), and the type of hanging (partial vs complete). Additional subgroup variables comprised the presence or absence of seizures, the presence or absence of cardiac arrest at presentation, and admission blood glucose levels categorized as <140 mg/dL vs ≥140 mg/dL.

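### The subgroup plan applies the main-analysis tests at 5% to six variables and names no treatment-by-subgroup interaction test, so it cannot show whether the effect differs between subgroups

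*Protocol article*

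**What the plan says.** The Subgroup Analysis section of the protocol article fixes the method by reference: "Subgroup analysis will be conducted using the same analytical methods described for the primary and secondary outcome measures". The sentence continues "including the subgroup variable and an appropriate effect size measure with a 95% CI".

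Six variables follow, each with two levels: sex, GCS (≤8 vs >8), type of hanging, seizures, cardiac arrest at presentation, and admission glucose (<140 vs ≥140 mg/dL).

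The methods referred to are in Analytical Statistics. Good neurological outcome "will be analyzed using the chi-square or Fisher exact test, with results expressed as relative risk estimates". A model is added: "The primary analysis will also adjust for GCS stratification at baseline using a multivariable regression model". Length of stay uses a t test or Mann-Whitney test. On the threshold, the section says "All statistical analyses will be carried out at a 5% level of significance"; only the interim analysis has a different one.

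Neither section mentions an interaction between treatment and subgroup, calls the subgroup results exploratory, or says how six variables are to be handled together.

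**The concern.** A subgroup analysis asks whether the treatment effect differs between, say, patients with GCS ≤8 and those with GCS >8. None of the stated methods answers that. The sentence can be read in two ways:

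- **Separate tests within each stratum.** This gives up to 12 P values for the primary outcome. Each asks whether there is an effect in that stratum; none compares the two strata.
- **The subgroup variable added to the regression.** Without a product term this is only a main effect, and the model still has a single common treatment effect. For GCS it would repeat the primary model, which already contains the GCS stratum.

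Under the first reading the risk is practical. Strata are small, so one half of a split will often reach P<.05 and the other will not, even when the effect is the same in both. The article expects its results to guide practice and guidelines, and such a split by GCS, sex or glucose could be taken as grounds for selective use.

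A smaller point is timing. The article writes "Additional subgroup variables comprised the presence or absence of seizures, the presence or absence of cardiac arrest at presentation", then admission glucose. Seizures have no clear time anchor of their own. In Summary Statistics they appear in a list that also holds ventilation, vasopressor support and in-hospital complications, some of which can arise after randomization.

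**Working it through.** **Inputs from the article (Sample Size):** 75% vs 55% good outcome, 80% power, 86 per arm before and 96 per arm after 10% attrition, 1:1 allocation. The two-sided level is taken as 5%, as in Analytical Statistics; the 0.05% printed in Sample Size does not give 86. **Not in the article:** subgroup prevalences. These are assumed, with the smaller stratum holding 20% to 50% of patients.

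**1. The plan's own figure.** n = (1.96 + 0.8416)² × (0.75×0.25 + 0.55×0.45) / 0.20² = 7.849 × 0.435 / 0.04 = 85.4, so 86 per arm; 86/0.9 = 95.6, so 96. Reproduced.

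**2. Power within a stratum at the planned effect.** Power = Φ[(0.20 − 1.96·√(2×0.65×0.35/n)) / √(0.435/n)].
- Half-size stratum, n = 48 per arm: (0.20 − 1.96×0.0974)/0.0952 = 0.096, power 54% (49% at 43 per arm).
- 30% stratum, n = 29 per arm: (0.20 − 1.96×0.1253)/0.1225 = −0.37, power 36% (32% at 26 per arm).

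**3. Chance that one variable is significant in one stratum only, same true effect in both.**
- No effect: 2 × 0.05 × 0.95 = 9.5%.
- Planned effect, 50/50 split: 2 × 0.54 × 0.46 = 50%.
- Planned effect, 70/30 split (powers 68% and 36%): 0.68×0.64 + 0.36×0.32 = 55%.

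**4. All six variables.** With 12 independent tests and no effect, the chance of any significant stratum is 1 − 0.95¹² = 46%. This overstates it, because strata of different variables share the same patients. It was therefore simulated: 86 or 96 per arm, six variables independent of each other and of outcome, uniform true effect, uncorrected chi-square at 5% in each stratum.

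| True effect, same in all strata | At least one variable significant in one stratum only |
|---|---|
| None | about 32-34% |
| Half (65% vs 55%) | about 58-61% |
| Planned (75% vs 55%) | about 86-95% |

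Ranges cover the assumed prevalences and both sample sizes.

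**5. What interaction tests would do.** Six independent tests at 5% with no true interaction: 1 − 0.95⁶ = 26.5%. Simulation gives roughly 20-34%, depending on the test and the prevalences; a Wald test on risk differences sits at the upper end. The figure barely depends on whether the drug works, whereas the stratum-test figure rises steeply with the true effect. With no drug effect at all, the gain is small.

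**6. Power for interaction.** For a 50/50 split the standard error of the difference between two stratum effects is twice that of the overall effect: 2 × √(0.435/96) = 0.135. If the effects truly differ by 20 points, power is about Φ(0.20/0.135 − 1.96) = Φ(−0.47) = 32% (29% at 86 per arm), taking the same outcome variance in both strata.

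**The case against.** The strongest reply is that the article never says strata will be tested separately. The sentence goes on to say that the subgroup variable is included, which fits the regression better than a chi-square test, and an interaction term may be what was meant. A separate analysis plan, not shown, may say so, and an article may leave such detail to it. Effect sizes with 95% CI are already promised, and nowhere does the article plan to compare significance across strata.

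Much of this stands. Stratum-level testing is a likely reading, not a stated one, and the figures in the table apply only under it. What does not stand is that this is mere silence. The article chooses a method by reference, that method contains no comparison of effects, and the 5% rule covers all analyses. The more favourable reading, a main effect in the regression, does not compare effects either.

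Three stronger inferences are tempting, and the document supports none of them:
- **A misleading split is almost guaranteed.** That is so only near the planned effect, which the Limitations section itself concedes may be considered relatively high.
- **The seizure subgroup is defined after randomization.** The words at presentation may cover seizures as well as cardiac arrest. This is an ambiguity, not a shown error.
- **Interaction tests remove the false signals.** Six unadjusted tests still leave roughly 20-34%.

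**Conclusion.** The concern holds in this form: the stated subgroup methods, at P<.05 and with no interaction test or exploratory label, cannot show whether the effect of dexamethasone differs between subgroups. This follows from the text under either reading.

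The size depends on assumptions. If the tests are run within strata and the effect is uniform, a one-stratum-only result for at least one variable is expected in about 86-95% of trials at the planned effect, about 60% at half of it, and about one in three with none. The prevalences are assumed, the six variables are taken as independent, and only the primary outcome is counted.

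The primary analysis is not affected. The change should be made because a better method is available at almost no cost.

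**What to change.** Rewrite the Subgroup Analysis section as follows:

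- For each of the six variables, add the subgroup and the treatment-by-subgroup interaction to the GCS-adjusted regression for the primary outcome. For the GCS subgroup only the interaction is new.
- Report the interaction P value and stratum-specific relative risks with 95% CI. Give no within-stratum P values.
- Label all subgroup results exploratory and exempt them from the general P<.05 rule.
- State that interaction power is low and that six unadjusted interaction tests carry roughly a 20-34% chance of at least one false signal.
- State that the seizure subgroup counts only seizures before randomization.

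If the analysis plan already contains these points, the article's sentence should be brought into line with it.

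The cost is wording, plus a check that seizure timing is captured on the case report form. No extra patients are needed. The Results section reports 3 patients enrolled at submission, so the change can be made well before the interim analysis at 50% enrollment. The drawback is that real differences between subgroups will usually be missed; that is a limit of 192 patients, and within-stratum tests do not remove it.

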### Sample Size

The sample size was calculated to detect a clinically meaningful difference in the proportion of patients achieving a good neurological outcome (GOS 4‐5) at day 28 between the dexamethasone and placebo groups. In our previous retrospective study, approximately 75% of near-hanging patients with altered sensorium who received steroids achieved a good neurological outcome [17]. Using these data, the expected event rate in the intervention group was assumed to be 75% while a favorable neurological outcome rate of 55% was assumed in the placebo group, corresponding to an absolute treatment effect of 20%.

The sample size for this superiority trial with a binary outcome was calculated using a 2-sided α of 0.05% and 80% statistical power. Sample size estimation was performed using the Sealed Envelope online sample size calculator for binary superiority trials [27]. The calculated sample size was 86 participants per treatment arm. To account for an anticipated 10% attrition rate due to loss to follow-up or protocol deviations, the sample size was inflated to 96 participants per arm, resulting in a total sample size of 192 participants.

The effect size was chosen as a pragmatic compromise between clinical relevance and study feasibility. Near-hanging with altered sensorium is an uncommon emergency presentation, and, based on patient admissions at the 3 study sites, 190 to 200 eligible patients were expected to be recruited during the planned study period. For detecting a smaller treatment effect, we will require a substantially larger sample size that will not be feasible within the available study period and funding. Despite this, an absolute improvement of 20% in favorable neurological outcomes was considered clinically important because such a benefit would be expected to substantially influence clinical practice, whereas failure to demonstrate a benefit of this magnitude would provide evidence against the routine empirical use of corticosteroids in this population.

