### Data Safety and Monitoring Board

Given the interventional nature of this trial, an independent Data and Safety Monitoring Board (DSMB) has been constituted in accordance with JIPMER’s DSMB guidelines to oversee participant safety and trial conduct. A DSMB charter was developed prior to trial initiation. The charter details the composition of the committee, minimum quorum requirements, frequency of meetings, the structure of meetings (open and closed sessions), and the procedures for documentation, communication, and reporting of recommendations.

The DSMB comprises 3 independent members: one expert from each of emergency medicine, internal medicine, and biostatistics. A quorum of 2 members is required for DSMB meetings. The study statistician will be responsible for presenting the interim efficacy analyses, and a consolidated summary of all AEs and SAEs will be submitted for DSMB review. The DSMB will periodically review accumulated safety and efficacy data, including a planned interim review after 50% enrollment in each treatment arm. Based on its evaluation, the DSMB may recommend continuation of the study without modification, protocol modification, or early termination of the trial. All DSMB recommendations will be formally communicated to the principal investigator, who will subsequently report them to the Institutional Ethics Committee.

An interim analysis will be conducted after enrollment of 50% of the planned sample size. The Haybittle-Peto stopping rule will be applied, with statistical significance for early termination defined as a *P* <.002 at the interim analysis stage. However, the final analysis will retain a 2-sided *α* level of .05.

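### The Sample Size section prints the planning alpha as 0.05% instead of 5%; the stated 86 per arm and 80% power hold only at 5%

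*Protocol article*

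**What the plan says.** The Sample Size section of the protocol article assumes a good day-28 outcome in 75% of the dexamethasone group and 55% of the placebo group. It states that the size for this superiority comparison was "calculated using a 2-sided α of 0.05% and 80% statistical power", obtained from a named online calculator. The result is 86 per arm, raised to 96 per arm for 10% attrition, 192 in total.

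The level of the final test is given in two other places:

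- Analytical Statistics: "All statistical analyses will be carried out at a 5% level of significance, and a *P* value <.05 will be considered significant". The same paragraph reserves P<.002 for interim analyses.
- Data Safety and Monitoring Board: "the final analysis will retain a 2-sided *α* level of .05". For the interim look, the section has "statistical significance for early termination defined as a *P* <.002 at the interim analysis stage".

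**The concern.** An alpha of 0.05% is 0.0005, one hundredth of the .05 used in the other two sections. Alpha, power and number per arm are tied together by one formula once the two event rates are fixed, so a 100-fold change in alpha cannot leave the other two figures where they are. Either the alpha is misprinted, or the 86 per arm and the 80% power are wrong.

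The sample size statement is the justification for randomizing 192 patients. A reader, an ethics committee or a board member who enters the printed inputs into a standard two-proportion calculation will not get 86, and could conclude either that the calculation is faulty or that the trial is far too small. The documents' own numbers can settle which figure is wrong.

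**Working it through.** **Inputs**

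- Good outcome 75% (dexamethasone) and 55% (placebo), difference 0.20: Sample Size.
- Power 80%: Sample Size.
- Allocation 1:1: Randomization and Allocation Concealment.
- Attrition 10%: Sample Size.
- Alpha, two-sided: 0.0005 as printed in Sample Size; .05 in Data Safety and Monitoring Board, and the same 5% level in Analytical Statistics.

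**Formula** (two proportions, unpooled variance)

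n per arm = (z₁₋α/₂ + z₀.₈)² × [p₁(1−p₁) + p₂(1−p₂)] / (p₁−p₂)²

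The variance term is 0.75×0.25 + 0.55×0.45 = 0.1875 + 0.2475 = 0.435. Divided by 0.20² = 0.04, it gives 10.875.

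**Step 1. The plan's own figure, at alpha 0.05**

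(1.960 + 0.842)² × 10.875 = 7.849 × 10.875 = 85.4, rounded up to **86 per arm**. Attrition: 86 / 0.9 = 95.6, rounded up to **96 per arm**, **192 in total**. All three printed figures are reproduced.

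**Step 2. The same inputs at the printed alpha of 0.0005**

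(3.481 + 0.842)² × 10.875 = 18.683 × 10.875 = 203.2, rounded up to **204 per arm**. Attrition, rounding in the same order as the plan: 204 / 0.9 = 226.7, rounded up to **227 per arm**, 454 in total.

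**Step 3. Power of the planned numbers**

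Power = Φ(0.20 / √(0.435/n) − z₁₋α/₂)

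| n per arm | 0.20 / SE | Power at alpha 0.05 | Power at alpha 0.0005 |
|---|---|---|---|
| 86 | 2.812 | 80.3% | 25.2% |
| 96 | 2.971 | 84.4% | 30.5% |

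**Step 4. Could another common formula yield 86 at 0.0005?**

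| Alpha | Sides | Unpooled | Pooled | Continuity-corrected |
|---|---|---|---|---|
| 0.05 | 2 | 86 | 89 | 98 |
| 0.05 | 1 | 68 | 70 | 79 |
| 0.0005 | 2 | 204 | 211 | 221 |
| 0.0005 | 1 | 186 | 193 | 203 |

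No variant at 0.0005 comes near 86; the smallest is 186. The exact match is the unpooled, two-sided calculation at 5%.

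**The case against.** The strongest reply is that this is a percent sign too many and nothing more. The calculation was evidently run at 5%, since 86, 96 and 192 all follow from that level. The level for the final test is stated twice elsewhere, and the two statements agree. No one will recruit a different number or judge a P value differently because of the slip. All of that stands, and it limits the point to a correction of the text.

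It also rules out three stronger readings that a reader might infer:

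- *The trial is underpowered.* The 25% and 31% power figures arise only if 0.05% is taken as the level of the test. The two sections that set that level, and the 86 per arm itself, exclude this. The figures show that the printed set is inconsistent; they do not measure a real deficit.
- *The plan has two competing thresholds, so that a final P between .0005 and .05 would be significant under one section and not under the other.* The Sample Size section reports an input to a calculation already made. It sets no decision rule. An analyst with a final P in that range has one answer from the plan: significant at 5%.
- *The final threshold is stricter than the interim one.* This would follow only if the planning alpha were a decision rule. The plan applies P<.002 at the interim look and .05 at the end.

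What the reply does not remove is that the error sits in the statement of a key design parameter, in the section that justifies the trial's size, and makes that statement impossible to reproduce as written.

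**Conclusion.** The Sample Size section misstates the planning alpha by a factor of 100. At the printed value, the alpha, the power and the number per arm cannot all hold: 204 per arm would be needed instead of 86. At a two-sided 5% level, which is the one the trial will use, 86 evaluable per arm gives 80.3% power, and 96 per arm and 192 in total are correct.

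The conclusion is firm, because the contradiction lies within the document and the 5% reading returns the printed numbers exactly. It rests on two assumptions. One is that the calculator used the unpooled formula; this is inferred from the exact match, as the article does not give the formula. With a pooled variance at 5%, the requirement would be 89 and the power of 86 per arm 79.0%, which does not change the conclusion. The other is that the event rates are taken as the plan states them; whether they are realistic is a separate question.

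**What to change.** In the Sample Size section, replace the printed alpha with: a two-sided α of 0.05 (5%). The section then agrees with Analytical Statistics, with the Data Safety and Monitoring Board section, and with 86, 96 and 192.

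If the same figure stands in the full protocol, which is not shown here, it should be corrected there too. The cost is one figure. Enrolment, the interim rule and the final analysis stay as they are.
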